### Recruitment

Recruitment will be conducted by the investigators of the Organization for Rural Community Development (ORCD) in Bangladesh (www.orcdbd.org). The ORCD is a local non-government organization involved in providing health services to rural people and conducting research. The ORCD investigators, and trained data collectors, will communicate with the potential participants over the telephone or by direct contact. The ORCD participants are not involved in the study design, but they will be involved in the recruitment and conduct of the study. Upon establishment of contact with eligible participants, the baseline data collection will be done through household visits. At household visits, the ORCD investigators and the data collectors will briefly explain the study objectives and their voluntary participation in the project. Interested potential participants will be assessed for eligibility that includes the measurement of blood pressure. Informed written consent will be obtained from all participants. Upon enrolment, a face-to-face interview will be conducted to collect information and record blood pressure from the participants whilst maintaining a social distance. Recruitment will stop once the required number of participants are enrolled. If we are unable to recruit completely from the original cohort, we will expand and recruit participants from outside of this specific cohort but from the exact location. Recruitment from outside of the proposed cross-sectional cohort is not expected to affect the primary objectives. Our source population is over 1000 participants. We do not anticipate any problems in recruiting 300 participants.

### Cluster randomization

Randomization will be performed after the recruitment of all participants and the baseline data collection. The entire 18 villages will be divided into two clusters: one cluster is with nine villages, about 50% of the study location, and the other cluster is with the remaining nine villages. The clusters are the unit of randomization. Each cluster has 150 participants; 10 to 20 participants are from each village based on the village size within a cluster. The intervention and the control group will not be divided into mutually exclusive groups based on risk factors for high blood pressure. This is because (i) this is highly likely that both clusters will have similar risk factors for high blood pressure and (ii) the intervention will be more practical given the nature of the intervention where participants will work as a team formed in different villages.

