### Sequence generation

Statistically, a simple random sampling technique (an unbiased coin toss) will be used to select the intervention group. The cluster is the unit of randomness but not the individual participants within clusters. However, within a cluster, we will aim to recruit participants with a male to female ratio equivalent. In that case, the restriction is to recruit one male after recruiting one female participant to make the sex ratio equivalent. Therefore, no random sequence will be generated. However, the complete list of potential percipients with hypertension is available from the previous cross-sectional study [15]. The study location, participants, and their socioeconomic condition can be accessed from the Narail district statistics [40].

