### Statistical analyses

Although the intervention will be conducted as clusters, data will be collected as individuals within clusters and the effect of the intervention will be measured based on individual’s data. Since the randomization is based on clusters, there might occur differences in baseline characteristics of participants. The baseline characteristics for the intervention and the control group will be examined using the chi-square test or Fisher’s exact test for categorical variables and the two-sample *t-*test or Mann-Whitney U test for continuous variables depending on the distributions of the data.

The effect size will be the mean difference in the primary outcome. The comparison will be made between differences for control and intervention groups after the follow-up. More specifically, it could be shown as the difference between DifCon and DifInt. DifCon equals the difference between baseline and follow-up for the control group, and DifInt equals the difference between baseline and follow-up for the intervention group. Such comparison will give the actual effect size due to the intervention. Generalized linear model (GLM) will be used for analytical purpose, and the models will be adjusted for factors which are different between control and intervention groups at baseline. For the secondary outcomes (motivation to smoking cessation, change in dietary patterns, and physical activity), chi-square tests will be used to detect any associations in the outcome variables across gender, age categories, level of education, and socioeconomic status. The difference in proportion with 95% confidence interval between control and intervention groups will be computed using the test of proportion, and odds ratios (OR) with 95% confidence interval will be computed using logistic regression techniques. The models will be adjusted for covariates as appropriate.

Rasch analysis using RUMM30 software will be used to investigate the psychometric properties of the Health Literacy tool and to compute the overall score from the 12-item HLS-Q12 tool. Individual item, as well as the overall score from all items combined, will be compared for gender, age group, level of education, occupation, and SES using chi-square, *t*-tests, or ANOVA as it is appropriate.

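### One coin toss between two nine-village blocks leaves one randomised unit per arm, so the trial yields no valid standard error or p-value for a randomised effect

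*Protocol article*

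**What the plan says.** All of this is in the protocol article.

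- **Cluster randomization.** The villages are merged before allocation: "The entire 18 villages will be divided into two clusters: one cluster is with nine villages, about 50% of the study location". The remaining nine villages form the other cluster, and "The clusters are the unit of randomization". On size: "Each cluster has 150 participants; 10 to 20 participants are from each village based on the village size within a cluster". Allocation follows recruitment and baseline data collection.
- **Sequence generation.** The mechanism is that "a simple random sampling technique (an unbiased coin toss) will be used to select the intervention group". The section adds that "The cluster is the unit of randomness but not the individual participants within clusters", and that no random sequence is produced.
- **Statistical analyses.** The analysis is at the level of the person: "data will be collected as individuals within clusters and the effect of the intervention will be measured based on individual’s data". It compares the change from baseline in the two arms using a generalized linear model, adjusted for factors that differ at baseline. The section states that this comparison gives the real effect of the intervention. It also accepts that "Since the randomization is based on clusters, there might occur differences in baseline characteristics of participants".
- **Abstract and Methods.** The study is called a cluster randomized controlled trial.

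The article does not say how villages are assigned to the two blocks.

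**The concern.** Randomisation supports a causal conclusion in two ways: it balances the arms on average, and it supplies the error against which the observed difference is judged. The second needs replication of the randomised unit within each arm. Here each arm holds one unit. Anything that makes blood pressure move differently in one block over the six months is then part of the estimated intervention effect, and the data contain no measure of how large such movements usually are.

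At stake is the primary conclusion. The article plans an inference about a 5 mmHg effect on systolic pressure at the 0.01 level, and attributes the between-arm difference in change to the intervention. More participants per block make each block mean more precise but add no randomised units. A later analysis plan could not repair this, because the missing replication lies in the allocation.

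**Working it through.** **Inputs from the article.** Two clusters of nine villages; one coin toss; 150 recruited per arm; 106 evaluable per arm; SD 12 mmHg; difference 5 mmHg; significance level 0.01 (sidedness not stated, two-sided assumed). No ICC is given, so every ICC below is an assumption.

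**The plan's own figure.** The stated 106 per group for 95% power does not reproduce for a two-group comparison: the usual formula gives 206 per arm two-sided, and 106 per arm gives about 68% power. That is a separate matter. Here 106 is used only as the planned evaluable number.

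**1. Degrees of freedom.** Clusters minus arms: 2 − 2 = 0. The between-cluster variance cannot be separated from the treatment effect.

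**2. Randomisation test.** There are C(2,1) = 2 allocations. The smallest p-value is 1/2 = 0.5 one-sided and 2/2 = 1.0 two-sided. Steps 1 and 2 need no ICC.

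**3. Can the model recover this?** A random effect for two blocks cannot be estimated alongside the treatment effect. A random effect for village would treat villages as if they had been randomised, which they were not.

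**4. Illustration: ICC between blocks.** Design effect DE = 1 + (106 − 1) × ICC. Actual size of the individual-level test = 2 × [1 − Φ(2.576/√DE)]. SD of the block difference = 12 × √(2 × ICC).

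| Assumed block ICC | DE | Actual size at nominal 0.01 | SD of block difference (mmHg) |
|---|---|---|---|
| 0.001 | 1.105 | 1.4% | 0.5 |
| 0.005 | 1.525 | 3.7% | 1.2 |
| 0.01 | 2.05 | 7.2% | 1.7 |
| 0.02 | 3.10 | 14.3% | 2.4 |
| 0.05 | 6.25 | 30.3% | 3.8 |

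If the naive standard error uses only the within-block variance, the last row becomes 31.5%. Hence 30–32%.

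**5. Illustration: ICC between villages, villages independent.** Each block effect averages nine villages, with 106/9 = 11.8 people per village.
- ICC 0.005: DE = 1 + 10.8 × 0.005 = 1.05, size 1.2%.
- ICC 0.05: DE = 1 + 10.8 × 0.05 = 1.54, size 3.8%.

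**6. Randomising the 18 villages 9:9.** Degrees of freedom are 18 − 2 = 16. There are C(18,9) = 48,620 allocations, so the smallest two-sided p-value is 2/48,620 = 0.00004. With 150 evaluable per arm, there are 150/9 = 16.7 per village and SE = 12 × √(2 × DE/150). Power is from the noncentral t distribution with 16 df:

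| Assumed village ICC | DE | SE (mmHg) | Power at 0.01 | Power at 0.05 |
|---|---|---|---|---|
| 0.01 | 1.16 | 1.49 | 67% | 88% |
| 0.02 | 1.31 | 1.59 | 60% | 84% |
| 0.05 | 1.78 | 1.85 | 44% | 72% |

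At the article's 40% loss (300 × 0.6 = 180, or 90 per arm), power at 0.01 falls to about 43%, 39% and 31%.

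**The case against.** The design has real merits. Allocating after recruitment and baseline guards against differential recruitment. The coin toss prevents a deliberate choice of the intervention block and is unbiased over hypothetical repetitions. The article also gives a practical reason for its arrangement, since participants work in village teams. All of this stands, but none of it adds a second unit to either arm.

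Several stronger readings are tempting, and the article does not support them.

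- *Every pre-existing difference between the blocks is inseparable from the intervention.* This goes too far. The change-from-baseline comparison removes stable differences in blood pressure level, and adjustment addresses measured factors. What remains is block-specific change and unmeasured factors. Local events, pandemic measures or different measurement staff are possible examples, but the article reports no such difference between blocks.
- *The article defends two clusters by asserting similarity, then contradicts itself.* The statement that "this is highly likely that both clusters will have similar risk factors for high blood pressure" is offered as a reason for not dividing the groups by risk factor. It is also compatible with the later concession that baseline differences may occur.
- *The blocks are two geographic halves of the Union.* Neither contiguity nor the grouping rule is stated.
- *The false-positive rate will be about 30%.* That needs a block-level ICC of 0.05, for which the article gives no basis. Under independent villages, the same ICC at village level gives about 4%. Geographic correlation would raise that figure by an unknown amount.

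**Conclusion.** The point holds, limited to the lack of replication. With one randomised unit per arm, the intervention is aliased with the village block. There are zero between-cluster degrees of freedom and no attainable two-sided randomisation p-value below 1.0. These results follow from the stated design alone. The individual-level comparison can describe how two village blocks differed in change. It cannot support a randomised causal claim unless block-specific change is assumed negligible, and the trial's data cannot test that assumption.

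The error-rate figures are illustrations only. They assume an SD of 12 mmHg applied to the outcome, 106 evaluable per arm, a two-sided 0.01 test and an ICC that the article does not supply. They run from about 1.2% to 32% according to that assumption, and the conclusion does not rest on them.

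**What to change.** Keep allocation after recruitment and baseline, but randomise the 18 villages individually, nine to each arm. Constrain or match the allocation on village mean baseline systolic pressure and village size, both known by then. Form teams within villages as far as possible, and analyse with village as the cluster, on about 16 degrees of freedom.

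Costs:
- A protocol amendment and an allocation list before the intervention starts.
- More risk of contamination between neighbouring villages, which would dilute the effect. The constrained allocation can limit this but not remove it.
- Some regrouping of teams. The article plans at least ten teams of about 15, and nine intervention villages with 10 to 20 participants each will not map neatly onto ten teams.
- A restated power calculation. The change restores valid inference but does not deliver the stated 95% power: with 150 evaluable per arm and an assumed village ICC of 0.01 to 0.05, power at 0.01 is about 67% to 44%. Part of that shortfall comes from the separate sample-size discrepancy.

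If village randomisation is impossible, or allocation has already taken place, describe the study as a controlled comparison of two village blocks and drop the randomised causal claim. That costs only a change of wording.

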### Sequence generation

Statistically, a simple random sampling technique (an unbiased coin toss) will be used to select the intervention group. The cluster is the unit of randomness but not the individual participants within clusters. However, within a cluster, we will aim to recruit participants with a male to female ratio equivalent. In that case, the restriction is to recruit one male after recruiting one female participant to make the sex ratio equivalent. Therefore, no random sequence will be generated. However, the complete list of potential percipients with hypertension is available from the previous cross-sectional study [15]. The study location, participants, and their socioeconomic condition can be accessed from the Narail district statistics [40].

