#### Secondary outcomes

(i)Psychometric properties of the HLS-EU-Q12 [36] questionnaire which is a 12-item questionnaire and was developed and evaluated in European countries for measuring health literacy. There are no validated tools for measuring health literacy in Bangladesh where HLS-EU-Q12 could potentially be used. However, it is unknown whether all items are appropriate as in Bangladesh. Therefore, assessing the reliability and validity of the HLS-EU-Q12 tool is a secondary outcome. Psychometric properties of the HLS-EU-Q12 [36] will be assessed at baseline only.(ii)Level of health literacy at baseline. After assessing the psychometric properties, we may come up with all 12 items or remove one or two items. Based on the validated tool, we will estimate the health literacy among the participants with high blood pressure. The outcome measure will be the proportion of people who have different levels of health literacy such as above or below average. The level of health literacy will be estimated at baseline only.(iii)The proportion of the smoker who smoked at baseline and at 6 months, and the proportion of smokers who intend to quit or reduce smoking within 1 month or 3 months at baseline and achievement after the intervention. Time frame: (1) baseline and (2) immediately after the intervention (6 months).(iv)The proportion of people who take regular physical exercise and who intend to take part in physical activities. To measure this outcome, the GPAQ [42] tool will be used. The difference in the proportion of participants who take part in regular exercise was measured at baseline and at follow-up. Time frame: (1) baseline and (2) immediately after the intervention (6 months).(v)The proportion of people who use their own mobile phone, can read SMS, and have the intention to receive and pay for SMS for health information. Time frame: baseline only.(vi)Perception of and practice in raw salt consumption. The outcome measure is the proportion. Tool: a modified version of Q-MAT [43]. Time frame: (1) baseline and (2) immediately after the intervention (6 months).(vii)Perceived barriers and enablers in participating and adopting lifestyle modifications to manage blood pressure. This is descriptive information. The software NVivo will be used to investigate if there are any common themes of barriers which could intervene. Time frame: immediately after the intervention (6 months).

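### Enrolling about 300 of 1072 listed people without a random order puts the baseline-only proportions, above all mobile-phone use, at risk of selection bias if they are read beyond the trial participants

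*Protocol article*

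**What the plan says.** **How people are enrolled.** Under Recruitment, the local investigators and data collectors "will communicate with the potential participants over the telephone or by direct contact". Then "Interested potential participants will be assessed for eligibility that includes the measurement of blood pressure", and "Recruitment will stop once the required number of participants are enrolled". If the earlier cohort does not supply enough people, "we will expand and recruit participants from outside of this specific cohort but from the exact location". The protocol considers whether this last step affects the primary objectives, but not the secondary ones.

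**Quotas.** Cluster randomization sets 150 per cluster, and "10 to 20 participants are from each village based on the village size within a cluster". Under Sequence generation, "the restriction is to recruit one male after recruiting one female participant to make the sex ratio equivalent".

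**Random element.** The only one is the coin toss between two clusters of nine villages. For individuals the same section says: "Therefore, no random sequence will be generated. However, the complete list of potential percipients with hypertension is available from the previous cross-sectional study". The Participants section puts the list at 1072 people after the age limit.

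**Outcomes concerned.** Secondary outcome (v) is "The proportion of people who use their own mobile phone, can read SMS, and have the intention to receive and pay for SMS for health" information. Outcome (ii) is the proportion at each level of health literacy. Both are measured at baseline only.

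**Target population.** Secondary objective 2, the abstract and outcome (ii) refer health literacy to the participants, and the Discussion describes the mobile-phone data in the same way. One Discussion sentence goes further and presents the health literacy result as the status of rural people in the country.

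**The concern.** Randomisation protects a comparison between arms. It does nothing for a one-sample proportion, which is only as representative as the way the sample was obtained. Here 28% of a known list is enrolled, so there is ample room for the enrolled to differ from the listed.

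For outcome (v) the mechanism is direct: someone who can be telephoned is more likely to own a phone and to read SMS. The Participants section itself accepts that phone access varies, since it caps age at 75 for that reason. For health literacy the link is indirect, through interest in the study and ease of contact. Fixing the sexes at 1:1 may move both proportions further if the list has another sex ratio.

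At stake is the use of these figures. The Discussion says the findings will inform later interventions, and outcome (v) would be the natural input for a text-message programme. A confidence interval around a selected proportion would not reveal the selection.

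**Working it through.** **1. Plan's own figures.**
- Hypertension in the earlier study: 1242/3104 = 40.0%, as stated.
- Village quotas: 9 villages x 10 to 20 = 90 to 180 per cluster, which contains the stated 150.
- Sampling fraction: 300/1072 = 28.0%.

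The documents give no phone ownership, contact route or sex ratio of the list, so the bias itself cannot be computed. What follows is illustration.

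**2. Selection on phone use.** Let p be the true proportion and R the chance of enrolment of phone users relative to non-users. The expected estimate is pR / (pR + 1 - p). With p = 0.60 (assumed):

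| R (assumed) | Calculation | Estimate | Shift (points) |
|---|---|---|---|
| 1 | 0.60 / 1.00 | 60% | 0 |
| 1.25 | 0.75 / 1.15 | 65% | 5 |
| 1.5 | 0.90 / 1.30 | 69% | 9 |
| 2 | 1.20 / 1.60 | 75% | 15 |

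For assumed p of 0.3, 0.5, 0.7 or 0.8, the shift is about 3 to 6 points at R = 1.25, 6 to 10 at R = 1.5 and 9 to 17 at R = 2. An R below 1 would reverse the sign.

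**3. Comparison with sampling error.** A simple random sample of 300 at p = 0.60 has a 95% half-width of 1.96 x sqrt(0.60 x 0.40 / 300) = 5.5 points. With the finite-population factor sqrt(772/1071) = 0.849 it is 4.7 points. At R = 1.5 the shift of 9 points exceeds this; at R = 1.25 it is about equal.

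**4. Sex alternation.** With female share f on the list and male-female gap g, the unweighted shift is (0.5 - f) x g. For assumed f = 0.4 or 0.6 and g = 0.1 to 0.4, this is 1 to 4 points in size. It is 0 if f = 0.5.

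**5. What a random draw could deliver.** The list dates from 2013. The Participants section describes it as defined by 140/90 mmHg or medication, whereas eligibility is now 130/80 or medication. (The Background attaches the same 40% to 130/80, so the definition behind the list should be confirmed.) The list also lacks people who were under 30 in 2013, that is, those aged about 30 to 36 in 2020, and people from outside it may be added. A random order would therefore remove choice by the recruiter. With first contact by visit, it would also remove selection by contact route. It would not remove refusal, and it would not make the list a frame for everyone now eligible.

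**The case against.** **The target is mostly the participants.** A proportion stated for the 300 has no sampling error or bias, and most of the text is limited in that way. This stands. It confines the problem to wider readings, of which the document contains one explicit instance, on health literacy. For the mobile-phone outcome, where the mechanism is strongest, the Discussion keeps to participants.

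**The order of approach is not described.** A reader might infer that recruitment is first-come, or that the recruiter freely picks the easiest to reach. The text says neither, direct contact is allowed alongside the telephone, and the village quotas already spread the sample over all 18 villages by size. This stands against the stronger reading. It does not remove the stated facts that no random order is used and that enrolment stops at the target.

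**Trials normally recruit volunteers, and the quoted sentence stands under Sequence generation.** Lack of random sampling does not by itself bias the between-arm comparison of blood pressure. That is correct, and no such bias is claimed here.

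**The list is not a full frame.** Also correct (step 5). For that reason weighting to the list's sex and village mix should not be presented as giving an estimate for the rural population.

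**Phone access is part of the chosen population.** Only in part. The age cap makes phone use likelier but does not require it, and outcome (v) still asks who has a phone of their own.

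**Conclusion.** The point holds as a risk, and a minor one. Enrolment is non-random by stated design, and two baseline-only outcomes depend on who is enrolled. The risk matters when these results are carried beyond the 300 participants; it is clearest for outcome (v) and weaker for (ii).

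Neither size nor direction follows from the documents. Under an assumed 60% ownership and phone users 1 to 2 times as likely to be enrolled, outcome (v) would shift by 0 to 15 points, and by 0 if phone users are not enrolled preferentially. A reader might infer that the proportions are certainly inflated; the documents contain no data to show it. The primary blood pressure comparison is not affected by this alone.

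**What to change.** If recruitment is still open:

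- Sort the existing list at random within village and sex, and approach people in that order until each village quota is filled. The sex alternation can be kept.
- Make first contact by household visit, since baseline data are collected there anyway.
- Record the contact route and, where telephone contact was used, report outcome (v) by route.

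In any case, describe (ii) and (v) as results for trial participants, and bring the Discussion sentence on health literacy in the rural population into line with secondary objective 2.

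The cost is one random sort of a list already held, one data field, one small table, a change of wording, and some extra visits to people who are harder to reach. The sample size does not change. The protocol places recruitment between December 2020 and March 2021. If it is complete, only the reporting by route (where recorded) and the limited claim remain.
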